4.3.5. Drug/medical device overview

Information on the drug used in the trial is summarized below.

Name of drug used: Rocuronium bromide intravenous solution

Study drugs: Traditional formation rocuronium, 50 mg/5.0 mL (MSD K.K.), novel formation rocuronium (Maruishi Pharmaceutical Co., Ltd.)

Approval status in study subjects: Within legal use.

Indications: Muscle relaxation during anesthesia, muscle relaxation during tracheal intubation

Storage: Store at 2–8°C

Clinically significant adverse reactions: Shock, anaphylaxis, prolonged respiratory depression, bronchospasm

Other precautions: There are reports of hearing loss when other nondepolarizing muscle relaxants were administered in the same manner in critically ill neonates or infants.

1. Subject selection

The subjects selected for this study will be patients scheduled for elective surgery under general anesthesia and for whom there is a medical need for the injection of rocuronium. The inclusion and exclusion criteria are mentioned in the previous section (Subjects). A strong withdrawal response after injection of Eslax was clearly demonstrated in minors in previous studies, so the subjects in this study will include juveniles as well as adults.

In this study, legal representatives are defined as follows.

1. A person who has been voluntary appointed as a guardian, a person with parental authority, a guardian, or curator (if applicable).
2. A spouse, adult child, parent, adult sibling, adult grandchild, grandparent, other relative living in the same household, or a person considered to be the equivalent of one of these close relatives.

The following is stipulated for when a legal representative is allowed to give approval in this study.

1. It is objectively judged that the patient is incapable of giving valid informed consent.
2. The patient is a minor. However, the physician in charge will give a full explanation using language that is understandable to the minor patient as well as his or her legal representative, and obtain written consent from both the legal representative and the patient.

Comprehensive assessment of the burden on subjects and the predicted risks and benefits, and measures to minimize the said burden and risk

Comprehensive assessment of the burden and predicted risks and benefits

Burden:

The use of rocuronium formulations is essential when administering general anesthesia, and the disadvantages associated with use of Eslax will not be increased in this clinical trial. In addition, the rocuronium formulation used in this clinical trial is procured using research funds, and will not be an economic burden on the patients themselves.

Risks:

Adverse effects of injection of rocuronium formulation

In a clinical trial in Japan on commercially available Eslax, 32 adverse effects (including abnormal clinical laboratory values) were reported in 18 (3.9%) out of a total of 461 patients. The main adverse effects were fluctuations in clinical laboratory values in 13 cases (2.8%), effects related to heart problems in 3 cases (0.7%), and effects related to vascular problems in 2 cases (0.4%). There is concern that adverse effects will appear at about the same level even with the new drug. However, assuming that a rocuronium formulation will be needed for general anesthesia even without participation in this clinical trial, there would be no increased risk to patients from participation in this trial.

Adverse events associated with observations during the trial

Observation of patients during this clinical trial is limited to the range of observations normally performed during general anesthesia.

Benefit:

Participants in this study will be presented with a gift certificate worth 1,000 yen.

1. Measures to minimize burden and risk

Patients’ conditions will be closely watched during the clinical trial, and utmost care will be taken to minimize the occurrence of adverse events. If an adverse event does occur, it will be dealt with appropriately.

7. Reparation for damage to health, and details of that reparation (in case of study involving invasive procedures)

In case of detrimental health effects in subjects due to adverse effects of the new drug or Eslax injected for this investigation, compensation shall be made using insurance purchased for the study.

8. Handling related to the provision of medical care to study subjects after the study is conducted (in cases when study is accompanied by medical acts that exceed normal treatment)

Patients’ health conditions will be closely observed after completion of the study, and in cases when treatment is necessary it will be provided at our hospital.

9. Evaluation and reporting of adverse events (in cases when study is accompanied by invasive procedures)

Adverse events in this study include all undesirable or unintentional signs, symptoms or diseases that occur during the performance of anesthesia, regardless of whether these events are causally related to the injection of rocuronium formulations.

When an adverse event is judged to have occurred, the name of the event, date of occurrence, severity and outcome will be recorded in the patient’s medical records. When an adverse event occurs, follow-up will be conducted until normalization, recovery, or remission to the level where the condition is no longer considered to be abnormal. Preceding events that continue during performance of anesthesia and events associated with the primary disease will be reported as adverse events only if they are exacerbated during anesthesia.

Serious adverse events in this study are defined as conditions that require hospitalization for treatment, and conditions in which there is impairment or concern of impairment. In cases when a serious adverse event is seen, a judgment will be made as to whether it is a known event described in point 6: “Measures to comprehensively evaluate the burden on subjects, as well as the predicted risks and benefits, and to minimize the said burden and risk,” or whether it is something unknown. When an adverse event occurs, the principal investigator will report it to the university president in accordance with the Kyoto Prefectural University of Medicine Serious Adverse Event Handling Manual.

10. Handling of personal information

The principal investigator (Associate [name]) will manage subject specimens or other materials by attaching a number (registration number) issued at the time of case registration that is unrelated to the personal information of the subject. When handling specimens or other materials relevant to this study, sufficient care will be taken to protect the confidentiality of the subject (anonymization).

When the correspondence table or other information is managed on a computer, it shall be done with the computer isolated from any network. When the results of the study are made public, they shall not include any information that can be used to identify subjects. Subject specimens and other materials obtained in the study shall not be used for any other purposes.

11. Procedure for receiving informed consent

Obtaining informed consent

A full explanation using the attached explanatory documents will be given to patients during an outpatient visit prior to surgery requiring anesthesia. Written consent is obtained at the discretion of the subject or legal representative. If the patient is 15–19 years old, written consent shall be obtained from both the patient and legal representative. If the patient is under 15 years old and informed consent is obtained from his or her legal representative, the patient’s informed consent will be obtained when it is judged that the subject can express his or her own intention with regard to the study.

If there is any essential change in the objectives or content of the study, the changes will be explained again orally and in writing, and consent will be obtained.

12. Monitoring and auditing system and procedures

Monitoring

In this study, monitoring will be done to ensure that the study is conducted safely and according to protocol, and that data are collected properly. The person in charge of monitoring shall ascertain the state of progress of the trial and confirm compliance with the facility protocol by inspecting the collected patient records. Specific monitoring items and implementation procedures shall be set out in the monitoring procedure manual established before the start of registration.

Auditing

Auditing will not be done in this trial. However, in the event of serious concerns with regard to the study results and ensuring patient safety, the principal investigator shall designate a third party not involved in the trial who can audit the trial.

13. Methods of storing and disposing of specimens and information

Specimens collected and data obtained in this study will be stored appropriately in the Kyoto Prefectural University of Medicine Department of Anesthesiology for 10 years after the results of the study have been published, under the responsibility of Department [name]. After that time, they will be disposed of. Anonymized data collected for analysis and for which written consent has been obtained in advance shall be kept after that time for possible use in secondary research (meta-analysis, etc.). In cases when data are used in future research, approval will be obtained again from the Kyoto Prefectural University of Medicine Institutional Review Board.

14. Report content and method of reporting to the head of the research institution

The status of this study will be reported once a year to the university president under the ethics review application system.

If any serious concern arises from the perspectives of respect for the human rights of subjects or others, such as leak of information related to the study, or in terms of implementing the study, a report shall be made immediately to the university president.

15. Conflicts of interest related to studies at the research institution, such as research funding sources, and conflicts of interest related to studies by the researchers and others, such as individual profit

This clinical trial is sponsored by Maruishi Pharmaceutical Co., Ltd., and Fuji Pharma Co., Ltd., who will provide the necessary funding and materials (rocuronium formulations) for the study.

Approval has been obtained from the Kyoto Prefectural University of Medicine Conflict of Interest Committee with regard to the interests of parties in this study. In the event that there is a change in interests, approval shall be obtained after review by the Kyoto Prefectural University of Medicine Conflict of Interest Committee and Kyoto Prefectural University of Medicine Institutional Review Board

16. Method of disclosing information related to this study

This study is registered in the UMIN Clinical Trials Registry, and the content of the study has been disclosed (registration number: UMIN 000022300). An article describing the study results shall be prepared regardless of the nature of the results. The authors shall be selected through discussion between the principal investigator, co-investigators and other related parties, and the first author of the article will be decided. The principal investigator will be the contact person.

This protocol was approved by IRB of Kyoto Prefectural University of Medicine (May 19, 2017).

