• Evaluation at anesthesia: Administered drugs (traditional formation rocuronium, novel formation rocuronium), dosage, administration start date, presence of the arm withdrawal response and magnitude of the response (as evaluated by the blinded research member), heart rate (just before and 3 minutes after administration), systolic and diastolic blood pressure (just before and 3 minutes after administration), TOF ratio according to the muscle relaxation monitor (just before and 3 minutes after administration).

• Adverse events: Type of event, date of occurrence, seriousness, whether there was a causative association, outcome, date outcome was confirmed.

• Drop out information: Day of discontinuation, reason for discontinuation.

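### The protocol's only definition of a serious adverse event does not list death, life-threatening events or prolonged hospital stay, so some grave reactions can be classed as non-serious

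*Protocol*

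**What the plan says.** Section 9 of the protocol first sets a broad scope for adverse events, regardless of cause: "undesirable or unintentional signs, symptoms or diseases that occur during the performance of anesthesia". Serious adverse events in this study are then "defined as conditions that require hospitalization for treatment, and conditions in which there is impairment or concern of impairment". The wording is a definition with two criteria, and nothing marks them as examples.

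The classification has a consequence in the same section: "In cases when a serious adverse event is seen, a judgment will be made as to whether it is a known event". Point 6 is the reference for that judgement, and an event not covered there counts as unknown. The reporting sentence that follows is triggered by the occurrence of an adverse event, without the word serious. It says that the principal investigator "will report it to the university president in accordance with the Kyoto Prefectural University of Medicine Serious Adverse Event Handling Manual".

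Two other places bear on the definition. The data items in section 4.3.3 include, for each adverse event, "Type of event, date of occurrence, seriousness, whether there was a causative association, outcome, date outcome was confirmed". Section 4.3.5 lists for the drug "Clinically significant adverse reactions: Shock, anaphylaxis, prolonged respiratory depression, bronchospasm".

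**The concern.** A definition of seriousness should catch the gravest outcomes by its plain wording, so that the assessor does not have to interpret it at the moment of the event. This one names neither death nor threat to life. Events are counted while anesthesia is being given, to patients having scheduled surgery, and a criterion based on needing hospitalization may separate little in that setting. The reactions that the protocol itself singles out for rocuronium are acute and can be treated on the spot.

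What is at stake is the reliability of the seriousness record for a formulation with a changed buffer, given to subjects from 6 months of age. Its safety expectation is carried over from the existing product: the risk text in point 6 expects adverse effects at about the same level. If an event is not classed as serious when it happens, the known/unknown judgement is not required, and an analysis plan cannot later supply a judgement that was never made.

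**Working it through.** No arithmetic applies. The check sets the definition beside the events it has to classify and beside the other places that could supplement it.

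**Step 1: is there another definition?** Section 4.3.3 collects seriousness as a data item but does not define it. Section 4.3.5 lists clinically significant reactions without linking them to seriousness. Section 9 cites an institutional handling manual for reporting, but states its own definition for this study and does not defer to the manual for it. The two criteria in section 9 therefore stand alone.

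**Step 2: apply the two criteria.**

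| Event | Requires hospitalization for treatment | Impairment, or concern of it | Class under the wording |
|---|---|---|---|
| Death during anesthesia | Not by its wording | Not by its wording | Meets neither criterion |
| Shock, anaphylaxis, prolonged respiratory depression or bronchospasm, fully resolved in the operating room | Not necessarily | No impairment remains; concern is a matter of judgement, and the term is undefined | Can be classed either way |
| Event that lengthens an existing stay | Arguable; prolongation is not listed | Depends on the event | Can be classed either way |

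**Step 3: what follows from a non-serious class?** The event is still an adverse event under section 9. Its name, date, severity and outcome are recorded and it is followed up. Taken literally, the reporting sentence also covers it. Two things can fail: the seriousness entry in the data, and the known/unknown judgement, which section 9 requires only for serious events.

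**Step 4: the reference for known/unknown.** Point 6 summarises a Japanese trial of the existing product. Its main effects were laboratory changes (13 cases), heart-related effects (3 cases) and vascular effects (2 cases). None of the four reactions in section 4.3.5 is named there. The same reaction can thus be a recognised one in section 4.3.5 and unknown by reference to point 6. This is a separate inconsistency between two sections. It errs on the cautious side, because an event judged unknown is not overlooked, so it does not add to the case on under-recognition.

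**The case against.** The strongest defence is that the second criterion includes concern of impairment. Shock or anaphylaxis can readily be judged to raise such concern, so a reader who infers that life-threatening reactions are excluded goes too far. That objection stands: for these reactions the supportable statement is that they are not listed and can be classed as non-serious. It does not help with death, and it leaves two assessors free to classify the same resolved reaction differently.

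Other stronger readings are also unsupported:

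- *A prolonged stay can never count.* The hospitalization criterion does not say new admission. A patient kept in hospital to treat an event could be said to require hospitalization for treatment. The protocol also does not state that all subjects are inpatients. Prolongation is unlisted, but it is not ruled out.
- *Grave events go unreported.* The reporting sentence is triggered by any adverse event, so a death or anaphylaxis may still reach the university president. However, routing every adverse event through a manual for serious ones leaves the intended trigger unclear.
- *The between-arm count of serious events will be too low.* The protocol lists no safety endpoint, and its statistical section names no safety comparison. There is no specified count to bias.

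Finally, the institutional manual is not shown and may contain fuller criteria. That limits certainty about what happens in practice. It does not alter the definition that the protocol sets for itself.

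**Conclusion.** The point holds as one of classification. The stated definition leaves out death, life-threatening events and prolongation of stay, and nothing else in the protocol adds them. For death the gap is plain. For the four reactions in section 4.3.5 it is a matter of discretion under an undefined term: all four can be classed as non-serious if they resolve in the operating room.

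No numerical size can be given, since the protocol states no expected rate for these events. The conclusion rests on reading section 9 as a closed definition, which its wording supports, and on the institutional manual not overriding it, which the protocol does not say. The primary and secondary efficacy inferences are unaffected. The amendment should be made, because the correction is cheap and the seriousness judgement cannot be reconstructed reliably afterwards.

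**What to change.** Amend the definition in section 9 so that a serious adverse event expressly includes one that results in death, is life-threatening, requires or prolongs hospitalization, causes impairment or concern of impairment, or is otherwise medically important. Give the reactions listed in section 4.3.5 as examples.

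In the same amendment, reconcile the point 6 reference for known/unknown with section 4.3.5, so that the two sections agree on which reactions are recognised.

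The cost is one paragraph and possibly a few more serious-event assessments. No treatment, endpoint, sample size or efficacy analysis changes.
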